### Eligibility criteria

The inclusion and exclusion criteria for the MASTER trial are shown in box 1.

Box 1Inclusion and exclusion criteria of efficacy and safety of the MASTER trialInclusion criteriaInformed consent by signature.Older than 18 years old.Acute ischaemic stroke (stroke onset within 7 days of randomisation).Contralateral, unilateral, incomplete upper limb paresis.Unilateral motor impairment with a Fugl-Meyer Upper-Extremity Score of less than 63/66.Residual voluntary finger extension of at least 10°.Exclusion criteriaPregnancy or lactation or positive pregnancy test in women of childbearing age (due to contraindication of maraviroc).Prestroke handicap with modified Rankin Scale >2.Diseases affecting motor function (eg, Parkinson’s disease, amyotrophic lateral sclerosis, amputation).Participation in another study with an investigational medicinal product within 30 days of randomisation.Enrolment of the investigator, his/her family members, employees and other dependent persons.Known hypersensitivity or allergy to maraviroc, peanuts, soy and/or mannitol.History of significant liver disease, hepatitis, elevated liver function tests (greater than 1.5 times the upper limit of normal).History of significant renal disease or end stage renal disease/dialysis, acute renal injury, creatinine clearance of less than 30 mL/min/1.73 m^2^.Patients with cardiovascular comorbidities and risk for orthostatic hypotension (eg, symptomatic heart failure, active coronary disease).HIV infection.Concomitant use of strong CYP3A4 inhibitors.Concomitant use of strong CYP3A4 inducers.MASTER, Maraviroc for Stroke Recovery.

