### Blinding and randomisation

Trial participants, care providers, outcome assessors, investigators and the study team will be blinded to treatment allocation throughout the trial. Blinding is maintained by the pharmacy of the Clinical Trial Unit (CTU), which prepares identical capsules containing either maraviroc 150 mg or placebo, indistinguishable in appearance and packaging. Each treatment bottle is labelled with a unique randomisation number. All trial data are managed through the SecuTrial clinical database, which is fully blinded to treatment assignment. Study unblinding will occur only after database lock and validation of the final statistical analysis plan by the investigators and sponsor. Unblinding of an individual participant’s allocation is only permitted in the event of a serious adverse event (SAE), when knowledge of the treatment arm is essential for clinical decision-making.

Randomisation (1:1) will be conducted by an independent statistician from the CTU at the Geneva University Hospital. A computer-generated list will be created using random permuted blocks of variable sizes (2, 4 and 6) to ensure allocation concealment. Stratification will be performed by:

Side of infarct (left vs right hemisphere)Degree of finger extension (Fugl-Meyer Extension Subscore: 1 or 2 points)

This results in four randomisation strata, ensuring balance across treatment arms with respect to the laterality and severity of motor impairment.

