### Data collection and management

All outcomes will be assessed using standardised procedures by trained personnel. Data will be collected at baseline and at 30, 60, 90 and 180 days poststroke. Participants who discontinue the intervention will be encouraged to complete all assessments. When in-person visits are not feasible, alternative follow-up (eg, home or phone visits) may be arranged. The patient timeline is shown in figure 1.

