### Primary outcome

#### Upper Extremity Fugl-Meyer Assessment score at 90 days poststroke

The Upper Extremity Fugl-Meyer Assessment (FMA-UE) will be conducted at all time points by trained occupational therapists or board-certified neurologists. This 0–66 point scale is widely used in stroke research for its reliability and sensitivity to change.^9^ The FMA-UE is a validated, reliable tool for assessing upper limb motor function in stroke patients.^9^ The minimal clinically important difference (MCID) is 12.4 points for patients with subacute, moderately severe stroke.^10^ All raters will undergo training before study initiation.

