### Statistical methods for primary and secondary outcomes

Two analysis sets will be used: an intention-to-treat population (all randomised participants who received ≥1 dose, analysed per allocation) and a per-protocol population (excluding those with major protocol deviations, eg, <80% medication adherence). Missing data will not be imputed.

The primary outcome (FMA-UE) will be compared between groups using a t-test or non-parametric equivalent. An adjusted analysis using multivariate linear regression will account for stratification variables (infarct side, finger extension ability) as well as other variables like CCR5-Δ32 loss-of-function mutation carrier status to account for confounding effects on motor recovery and treatment response. Secondary outcomes will be analysed via regression models adjusted for the same covariates. Linear mixed models will include time point and group as fixed effects and participant ID as a random effect to account for repeated measures. To assess whether maraviroc promotes recovery via peri-infarct plasticity, causal mediation analysis will estimate direct and indirect effects (via changes in connectivity/metabolism from baseline to 90 days). The analysis includes three regression steps, with the indirect effect tested via the Sobel method. Weekly rehabilitation hours (during the first 90 days) will be included as a covariate. A similar approach will be applied to motor learning outcomes. Safety analyses will summarise the number and proportion of participants with ≥1 SAE, AE of special interest, or death by day 90 in each group.

Analyses will be conducted in R, MATLAB or Python using appropriate packages. Imaging data will be processed with FSL, FreeSurfer, SPM and DSI Studio, depending on modality.

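### The primary day-90 FMA-UE comparison is unadjusted and no planned model names baseline FMA-UE, so the trial forgoes precision it could have at no cost

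*Protocol article*

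**What the plan says.** Under 'Statistical methods for primary and secondary outcomes' the protocol article describes three analyses that bear on FMA-UE.

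- **First-named comparison:** "The primary outcome (FMA-UE) will be compared between groups using a t-test or non-parametric equivalent". It has no covariates.
- **Adjusted linear regression:** it "will account for stratification variables (infarct side, finger extension ability) as well as other variables like CCR5-Δ32 loss-of-function mutation carrier status". Baseline FMA-UE is not named.
- **Mixed models:** "Linear mixed models will include time point and group as fixed effects and participant ID as a random effect". Neither a baseline covariate nor a group-by-time term is named.

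The baseline value will be available. In the primary outcome section, "The Upper Extremity Fugl-Meyer Assessment (FMA-UE) will be conducted at all time points", and under 'Data collection and management', "Data will be collected at baseline and at 30, 60, 90 and 180 days poststroke".

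On severity at entry, the eligibility box requires "Unilateral motor impairment with a Fugl-Meyer Upper-Extremity Score of less than 63/66", together with incomplete paresis and some residual finger extension. Randomisation is stratified by infarct side and by "Degree of finger extension (Fugl-Meyer Extension Subscore: 1 or 2 points".

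The motor-learning score is also measured at baseline and day 90. The secondary outcomes use regression with the same covariates as the adjusted FMA-UE analysis.

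**The concern.** When the outcome scale is measured at baseline, the baseline value usually predicts the later score. Leaving it out keeps differences in initial severity in the error term, so the treatment effect is estimated less precisely than the data allow. The FMA-UE total has an upper entry limit but no stated lower limit, so entry severity may vary a good deal.

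The strata raise a second issue. If randomisation balances the arms on prognostic factors and the analysis then ignores them, the t-test's standard error includes variation that the design has already removed from the comparison. The test is then conservative.

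At stake is how precisely a single-centre trial of 80 patients answers its main question, above all if the true effect is smaller than the large one planned for. The secondary motor-learning analysis has the same gap, since its own baseline score is not named as a covariate.

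**Working it through.** **Inputs from the article ('Sample size estimate').** Difference 12.4 points; SD 17.5; type I error 5%; power 80%; dropout or exclusion 20%. Allocation is 1:1. Missing data are not imputed, so 64 of 80 patients are analysed if 20% are lost. Sidedness is not stated; two-sided reproduces the plan's figure.

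**Inputs assumed.** The baseline to day-90 correlation r is not given, so 0.3 to 0.8 is shown. The share of variance explained by the strata is not given, so 10 to 30% is shown.

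**Step 1: the plan's own sample size.**
- n per arm = 2 × (1.96 + 0.8416)² × (17.5/12.4)² = 31.27, rounded up to 32.
- Total 64; 64/0.8 = 80. This is the stated figure, and it is built on an unadjusted two-group comparison.
- Standard error of the difference at 32 per arm = 17.5 × √(2/32) = 4.375, and 12.4/4.375 = 2.834. The noncentral t distribution with 62 df gives 79.7% power.

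**Step 2: adding baseline FMA-UE.** If 17.5 is the SD of the day-90 score, the residual SD is 17.5 × √(1 − r²). Power is from the noncentral t with 61 df at 32 per arm. The difference detectable with 80% power is (1.96 + 0.8416) × residual SD × √(2/32), a normal approximation.

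| r (assumed) | Residual SD | 12.4 / SE | Power at 12.4 points | Detectable difference |
|---|---|---|---|---|
| 0 | 17.50 | 2.834 | 79.7% | 12.3 |
| 0.3 | 16.69 | 2.971 | 83.3% | 11.7 |
| 0.5 | 15.16 | 3.273 | 89.6% | 10.6 |
| 0.6 | 14.00 | 3.543 | 93.7% | 9.8 |
| 0.7 | 12.50 | 3.969 | 97.4% | 8.8 |
| 0.8 | 10.50 | 4.724 | 99.6% | 7.4 |

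Using two further degrees of freedom for the strata (59 df) changes power by less than 0.1 percentage points.

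**Step 3: ignoring the strata.** If balanced strata explain a share R² of the variance, the true standard error of the difference is √(1 − R²) times the one the t-test uses. The actual two-sided type I error is then about 2 × [1 − Φ(1.96/√(1 − R²))].
- R² = 0.10: 1.96/0.949 = 2.07, giving 3.9%.
- R² = 0.20: 1.96/0.894 = 2.19, giving 2.8%.
- R² = 0.30: 1.96/0.837 = 2.34, giving 1.9%.

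Simulation of the t-test with 32 per arm and exactly balanced strata gives 3.8, 2.8 and 1.9%.

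**The case against.** The main points on the other side are these.

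- **Design and analysis agree.** The sample size was computed for the test that is planned, and that test delivers essentially the planned power. A reader might infer that the trial is underpowered or its estimate biased. The documents support neither: under randomisation the unadjusted comparison is valid, and the departure from 5% is on the conservative side. This stands.
- **The covariate list is open.** A reader might infer that baseline FMA-UE is excluded from the regression. The wording gives CCR5-Δ32 status only as an example of further variables, so the baseline is unnamed, not ruled out. The same holds for the motor-learning baseline. This stands for the regressions, but not for the first-named comparison, which has no covariates.
- **Severity is partly handled.** Finger extension enters both the randomisation and the adjusted regression, and mixed models are planned. This stands in part. A two-level subscore is a coarse substitute for the full scale. Without a group-by-time term, the mixed model's group effect as described is not a day-90 contrast.
- **The gain is uncertain.** At r = 0.3 it is under 4 percentage points. The finger-extension requirement may narrow the entry range and so lower r. If 17.5 is an SD of change, the residual SD formula does not apply. If the strata explain 30% of the variance, the t-test's own power rises to about 83% (simulated), which narrows the gap. All of this stands, so the gain can only be given as a range.
- **Chance imbalance.** A reader might attach a probability to a sizeable baseline imbalance under simple randomisation. That would not describe this trial, which uses permuted blocks within four strata.
- **T-test or rank test.** A reader might see two competing primary p-values. The rule for choosing is commonly left to the statistical analysis plan, and the article says a final one will be validated before unblinding. That is not counted here.

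**Conclusion.** The point holds as one of efficiency. The article fixes an unadjusted primary comparison that ignores both randomisation strata, and none of its models names a baseline measurement that every participant will have.

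The size depends on quantities the article does not give. If 17.5 is the SD of the day-90 score and r lies between 0.3 and 0.8, power for 12.4 points would rise from 79.7% to between 83% and 99.6% with the same 64 analysed patients. If the strata explain 10 to 30% of the variance, the t-test runs at about 4 to 2% instead of the nominal 5%. That baseline FMA-UE is the strongest predictor available is plausible, since it is the same scale, but the article does not show it.

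This is an improvement available at no cost, not an error that must be corrected for the trial to be valid.

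**What to change.** Before unblinding, in the protocol and the final statistical analysis plan:

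1. Make the primary analysis a linear model of day-90 FMA-UE on treatment, baseline FMA-UE, infarct side and finger-extension stratum, with a closed covariate list.
2. Report the adjusted mean difference with its 95% confidence interval. It is on the scale of the 12.4-point target, which a rank test does not estimate.
3. Keep the t-test or rank test as a sensitivity analysis.
4. Add the baseline motor-learning score to the motor-learning model.

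The cost is wording only. Baseline FMA-UE, the motor-learning baseline and both strata are already collected, so no new data or patients are needed. The sample size can stay at 80.

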**Methods and analysis:**

MAraviroc for STrokE Recovery is a phase II, single-centre, randomised, double-blind, placebo-controlled trial. The aim is to assess the efficacy and safety of the CCR5 antagonist Maraviroc for improving motor recovery of the upper limb after ischaemic stroke. 80 ischaemic stroke patients with moderate but incomplete upper extremity motor impairment will be enrolled within 7 days of onset. Participants will be randomised (1:1) to receive either oral maraviroc (300 mg two times per day) or placebo for 90 days in addition to standard rehabilitation therapy. The primary outcome is upper limb motor function assessed using the Fugl-Meyer Assessment for the Upper Extremity at day 90. Secondary outcomes include motor learning skills and plasticity in the peri-infarct region assessed using MRI connectivity and spectroscopy at 90 days.

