### Secondary outcomes

Motor learning score (ability of a subject to learn a finger tapping sequence task with the paretic hand) at 90 days poststroke.

The motor sequence learning task assesses procedural motor learning capacity, relevant to rehabilitation outcomes and has been validated in previous studies within our own group.^11^ It will be administered at baseline and at 90 days. It consists of a finger tapping task using a commercial five-button response box. Data will be collected digitally and stored securely for analysis.

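### The regression for the motor learning score does not name the score's own baseline, although that baseline is collected; naming it is a nearly free gain in precision

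*Protocol article*

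**What the plan says.** Under Secondary outcomes, the protocol article lists a single item: "Motor learning score (ability of a subject to learn a finger tapping sequence task with the paretic hand) at 90 days poststroke". Of the task it says: "It will be administered at baseline and at 90 days". A pre-treatment value of the same measure is therefore planned for every participant.

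Under Statistical methods for primary and secondary outcomes, the adjusted FMA-UE regression "will account for stratification variables (infarct side, finger extension ability) as well as other variables like CCR5-Δ32 loss-of-function mutation carrier status". The rule for secondary outcomes refers back to that list: "Secondary outcomes will be analysed via regression models adjusted for the same covariates". No baseline score of any outcome is named as a covariate.

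The next sentence adds a repeated-measures model: "Linear mixed models will include time point and group as fixed effects and participant ID as a random effect to account for repeated measures". It does not say which outcomes this model serves, or whether baseline counts as one of the time points.

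The abstract describes the secondary outcomes more widely: "Secondary outcomes include motor learning skills and plasticity in the peri-infarct region assessed using MRI connectivity and spectroscopy at 90 days". The body of the article places the MRI measures under Other outcomes.

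**The concern.** When a continuous outcome is measured before and after treatment, its own baseline is usually among the strongest predictors of the final value. Here the secondary-outcome rule borrows its covariates from a model for a different outcome. Even if baseline FMA-UE were added to that list, the borrowed rule would bring in baseline FMA-UE and still not the baseline motor learning score. The finger-extension stratum has two levels (1 or 2 points) and is at best a coarse stand-in for performance on a sequence-learning task.

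What is at stake is the width of the confidence interval and the power for this outcome. Patients will differ in the score before any treatment, and whatever part of that difference persists to day 90 stays in the residual variance. With about 32 evaluable patients per arm, a chance baseline difference between arms also carries into the day-90 comparison, in proportion to the slope of the day-90 score on baseline.

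**Working it through.** **1. The article's own figure.** Inputs from Sample size estimate: difference 12.4, SD 17.5, type I error 5% (sidedness not stated; two-sided reproduces the result), power 80%, dropout 20%. Allocation is 1:1 (Study design).

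- n per arm = 2 × [(1.960 + 0.842) × 17.5 / 12.4]² = 31.3, rounded up to 32
- Evaluable total = 64; 64 / 0.80 = 80

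The stated 80 reproduces. It rests on an unadjusted FMA-UE comparison, so the covariates of a secondary outcome do not affect it.

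**2. Inputs for the motor learning score.** The article gives no SD, target effect or baseline to day-90 correlation for this score. Assumptions:

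- 32 evaluable per arm, two-sided 5%
- Standardised effect of 12.4 / 17.5 = 0.709 (borrowed from FMA-UE), or 0.5
- Correlation ρ between baseline and day-90 score, after allowing for the other covariates, from 0 to 0.7

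**3. Formula.** ANCOVA on the baseline value multiplies residual variance by 1 − ρ², so the standardised effect becomes d / √(1 − ρ²). Power is from the noncentral t distribution. The last column is 64 / (1 − ρ²), the number of unadjusted patients carrying the same information.

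| ρ | 1 − ρ² | Power, d = 0.709 | Gain (points) | Power, d = 0.5 | Gain (points) | Equivalent n |
|---|---|---|---|---|---|---|
| 0 | 1.00 | 79.7% | – | 50.4% | – | 64 |
| 0.2 | 0.96 | 81.3% | 1.6 | 52.0% | 1.6 | 67 |
| 0.3 | 0.91 | 83.3% | 3.6 | 54.1% | 3.8 | 70 |
| 0.5 | 0.75 | 89.6% | 10.0 | 62.3% | 11.9 | 85 |
| 0.7 | 0.51 | 97.4% | 17.7 | 78.7% | 28.4 | 125 |

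A simulation at d = 0.709 (3,000 trials per ρ) agrees: about 80% unadjusted, against 83%, 89% and 97% with ANCOVA at ρ = 0.3, 0.5 and 0.7.

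**4. Does the mixed model already do this?** Suppose it is applied to this score with baseline and day 90 as the two time points. With time and group as main effects only, the group coefficient averages the difference between arms over both times. The expected difference is 0 at baseline and 0.709 at day 90, so the coefficient targets (0 + 0.709) / 2 = 0.354. The simulation gave 0.35 to 0.36. As written, the model therefore recovers about half the day-90 effect and does not estimate the day-90 contrast.

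**5. Missing baselines.** The article says that missing data are not imputed. If a share m of patients lacks a baseline score, a complete-case ANCOVA has effective size 64 × (1 − m) / (1 − ρ²). It breaks even with the unadjusted analysis at m = ρ²: 4% missing at ρ = 0.2, 9% at 0.3, 25% at 0.5.

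**The case against.** A reader might infer that the plan confines the regression to infarct side, finger extension and CCR5-Δ32 status and so excludes the baseline score. The text does not support that. The list is open ("as well as other variables like CCR5-Δ32 loss-of-function mutation carrier status"), and the article is a condensed account whose statistical analysis plan is still to be finalised before unblinding and is not shown. The accurate statement is that the article does not name the baseline score. What remains is that it does state a covariate rule for secondary outcomes, and that rule points to a list made for FMA-UE, where the baseline of a different measure would not be expected.

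The mixed model could bring the baseline score in as a time point. That is fair, but step 4 shows that the model as described would not give the day-90 contrast.

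The correlation may be low. The score is defined as ability to learn a sequence, and the scoring formula is not given. If it is a within-session gain, it is already relative to the patient's own starting level and may correlate weakly over 90 days. This objection stands, and it is why the size can only be given as a range.

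A reader might also infer bias, or that a baseline imbalance passes in full into the estimate. Neither follows. Allocation is randomised and stratified on side and finger extension, and an imbalance carries over only in proportion to the baseline to day-90 slope.

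Finally, calling this the only secondary outcome fits the Secondary outcomes section but not the abstract. If the MRI measures are secondary too, the same rule would govern them, and they also have a value at randomisation.

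**Conclusion.** The point holds as a free to cheap improvement. The article collects a baseline motor learning score, and its stated regression rule for secondary outcomes neither names that score nor would naturally include it. The loss is precision, and the sample size of 80 stands. For an assumed effect of 0.5 to 0.709 SD with 32 evaluable per arm, adjustment gains about 4 points of power at a correlation of 0.3, 10 to 12 points at 0.5, and under 2 points at 0.2 or below. These sizes rest wholly on an assumed correlation and effect, the upper effect being borrowed from FMA-UE. They show that the gain could be material, not that it will be.

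**What to change.** In Statistical methods for primary and secondary outcomes, state that each secondary-outcome regression includes that outcome's own baseline value together with the stratification factors. For the motor learning score, this is an ANCOVA of the day-90 score on group, baseline score, infarct side and finger-extension stratum.

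State also how patients without a baseline score stay in the analysis. One option is a constrained longitudinal model with a common baseline mean and a time-by-group term, whose day-90 contrast is the treatment effect. Another is a missing-baseline indicator in the ANCOVA. If the mixed model is kept for this outcome, name the outcome and add the time-by-group term.

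The cost is one clause, one or two degrees of freedom and a rule for missing baselines. No new data or visits are needed, and the change can be made blind, since the article has the final analysis plan validated before unblinding.

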**Figure 1 F1:**
[figure not shown]
Flow chart of the MASTER trial. V1 screening includes prescreening of patients for inclusion criteria and inclusion for additional screening of exclusion criteria. Randomisation occurs within 7 days of stroke onset. V2 includes randomisation and initial assessments (imaging and clinical), carried out within 24 hours of beginning of intervention medication. V3 and V4 include one clinical assessment. V5 is the primary outcome time point, including both imaging and clinical assessments. V6 represents the 180 days follow-up. Telephone check-ins occur between each in-person visit. MASTER, Maraviroc for Stroke Recovery; mRS, modified Rankin Scale; NIHSS, National Institutes of Health Stroke Scale; FLAIR, Fluid-Attenuated Inversion Recovery; DWI, Diffusion-Weighted Imaging; MRSI, Magnetic Resonance Spectroscopic Imaging.

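### The supporting mixed model names group and time point but no group-by-time term, so it yields neither a day-90 effect nor a difference in recovery

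*Protocol article*

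**What the plan says.** The model is stated in the Protocol article under Statistical methods for primary and secondary outcomes: "Linear mixed models will include time point and group as fixed effects and participant ID as a random effect to account for repeated measures". No interaction and no visit-specific contrast is named there or elsewhere in the article. The sentence follows the one on secondary outcomes and does not say which outcomes the model is for.

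The visit schedule is under Data collection and management: "Data will be collected at baseline and at 30, 60, 90 and 180 days poststroke". The FMA-UE "will be conducted at all time points by trained occupational therapists or board-certified neurologists" (Primary outcome). For the motor learning task, Secondary outcomes says: "It will be administered at baseline and at 90 days". The Figure 1 legend places the first assessment at the start of treatment: "V2 includes randomisation and initial assessments (imaging and clinical), carried out within 24 hours of beginning of intervention medication".

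The primary analysis is separate. The abstract says: "The primary outcome is upper limb motor function assessed using the Fugl-Meyer Assessment for the Upper Extremity at day 90". The statistical section says: "The primary outcome (FMA-UE) will be compared between groups using a t-test or non-parametric equivalent". An adjusted regression follows, which "will account for stratification variables (infarct side, finger extension ability) as well as other variables like CCR5-Δ32 loss-of-function mutation carrier status". Baseline FMA-UE is not among the covariates named.

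**The concern.** The hypothesis is that maraviroc improves recovery, meaning that the arms start together and then diverge. In a longitudinal model, divergence is carried by the group-by-time term, and the stated model has none. Its group term asks for one constant difference across all modelled visits. If baseline is one of those visits, the model forces a treatment effect onto an assessment made around the first dose, where randomisation makes the expected difference about zero.

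What is at stake is the reading of the secondary results. The article allows for 20% dropout or exclusion and will not impute missing data, so the t-test and the day-90 regression can use only patients with a day-90 value. The mixed model is the named analysis that could also draw on partial follow-up. As written, it answers a different question. A real day-90 effect could appear smaller in it and be read as disagreement with the primary result.

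**Working it through.** **Inputs.** Difference 12.4 points, SD 17.5, 5% type I error, 80% power, 20% dropout or exclusion (Sample size estimate); 1:1 allocation (Study design); visits at baseline, 30, 60, 90 and 180 days (Data collection and management). Assumed, because the article does not give them: a two-sided test, the trajectory of the effect, and a within-patient correlation ρ of 0.5 to 0.9.

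**1. The plan's own figure.** n per arm = 2 × (1.96 + 0.84)² × (17.5/12.4)², about 31.3, rounded up to 32. The total is 64, and 64/0.8 = 80. The stated 80 is reproduced, and it rests on a two-group comparison at day 90. With 32 per arm that comparison has 81% power (normal approximation) or 80% (t distribution).

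**2. What the group coefficient estimates.** In complete, balanced data, a random-intercept model with visit and group main effects has a group coefficient equal to the simple mean of the visit-specific group differences. For a true day-90 difference of 12.4:

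| Visits modelled as response | Assumed trajectory | Coefficient targeted | Share of 12.4 |
|---|---|---|---|
| Baseline, 30, 60, 90, 180 | Linear to day 90, then flat | (0 + 4.13 + 8.27 + 12.4 + 12.4)/5 = 37.2/5 = 7.44 | 60% |
| Baseline, 30, 60, 90, 180 | Full from day 30 | (0 + 4 × 12.4)/5 = 49.6/5 = 9.92 | 80% |
| Baseline, 90 | Any | (0 + 12.4)/2 = 6.2 | 50% |
| 30, 60, 90, 180 | Linear to day 90, then flat | 37.2/4 = 9.3 | 75% |
| 30, 60, 90, 180 | Full from day 30 | 49.6/4 = 12.4 | 100% |

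The baseline-and-day-90 row shows the halving on the FMA-UE scale. The article gives no planning values for motor learning.

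**3. Direction when baseline is included.** Under linear build-up, the first four visits sum to 0 + 4.13 + 8.27 + 12.4 = 24.8. For the five-visit mean to equal 12.4, the total must be 62, so the day-180 difference would have to be 62 − 24.8 = 37.2 points, three times the day-90 difference.

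**4. Power of the group test, 32 per arm.** The SD of a patient's mean over T visits is 17.5 × √((1 + (T − 1)ρ)/T). For ρ from 0.5 to 0.9:
- Five visits, linear then flat: 59% down to 43%.
- Five visits, full from day 30: 83% down to 66%.
- Baseline and day 90, taking the same standardised effect: 37% down to 31%.
- Follow-up only, linear then flat: 77% down to 60%.
- Follow-up only, full from day 30: 95% down to 84%.

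**5. Simulation check** (150 runs, 32 per arm, ρ = 0.7). The main-effects model gave mean coefficients of 7.5, 10.1 and 6.3 for the first three rows of the table. With the group-by-visit term added, the day-90 contrast averaged 12.2, 12.8 and 12.6, against a true 12.4.

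**The case against.** The strongest reply is that nothing primary depends on this model. That stands. The day-90 comparison, its type I error, its power and the sample size do not change. A reader might infer that the trial cannot test its hypothesis or is underpowered for it. The article does not support that, because the t-test and the adjusted regression address the hypothesis at day 90.

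A second reply is that baseline as a response is an inference. That stands for the FMA-UE: the article says when the scale is administered, not which visits enter the model as outcomes. A reader might take it as settled that a pre-treatment visit shares the treatment effect, but the wording only suggests it. For motor learning no inference is needed. With two assessments, any repeated-measures model must use baseline as a response. The article does not say, however, that the mixed model will be applied to motor learning, or to any other named outcome.

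Third, a visit-averaged effect is a legitimate target, and the article never calls this coefficient the day-90 effect. With follow-up visits only and a constant effect, nothing is lost and power exceeds that of the day-90 comparison. This limits the size of the problem. It does not supply a day-90 estimate or a test of differential recovery, and a constant effect from the first follow-up visit is the favourable case.

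Last, the article is condensed, saying what a model will include does not exclude other terms, and a final statistical analysis plan is to be validated before unblinding (Blinding and randomisation). That plan may add the interaction. But the article is not silent here: it lists the fixed effects and leaves out the one that carries the question.

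**Conclusion.** The point holds as a moderate defect in a supporting or secondary analysis. As stated, the mixed model gives one visit-averaged difference, with no day-90 effect and no difference in recovery. For a true day-90 difference of 12.4 points it targets about 7.4 to 9.9 if baseline is a response, half the effect for an outcome measured only at baseline and day 90, and about 9.3 to 12.4 with follow-up visits only.

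These sizes rest on complete, balanced data and on two assumed trajectories; the power figures also rest on an assumed correlation. A reader might quote a 40% understatement as the result. That is one scenario, and the article gives no trajectory to support it over the others. When baseline is included, understatement of the day-90 effect is the robust part. The point is not a must-fix, because the primary analysis and the sample size do not depend on it.

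**What to change.** Replace the sentence with one that:
- names the outcomes the model applies to;
- includes group, visit as a categorical factor, and the group-by-visit interaction;
- states how baseline enters, either as a covariate with follow-up visits as responses, or as a response with the arm means constrained equal at baseline;
- names the day-90 contrast as the treatment effect reported from this model.

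For an outcome measured only at baseline and day 90, the covariate form reduces to a regression of the day-90 value on group and baseline. The covariance structure and a day-180 contrast are optional choices.

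The cost is one sentence of analysis wording and no new data. Recruitment is planned to run to December 2027 and unblinding waits for the validated analysis plan, so the change can be made before any allocation is known.
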